## Abstract

**Background:**

Adolescence is a critical period for developing and maintaining good habits for mental health and well-being. This is crucial for future mental health; as most mental health problems emerge during adolescence. Mental health literacy forms the foundation for preventing mental health issues, reducing stigma, and enhancing the effectiveness of help-seeking, particularly among adolescents.

**Objective:**

This study aims to measure the effect of social media-based educational intervention on mental health literacy among male high school students in Ramhormoz city.

**Methods:**

This randomized controlled trial (RCT) evaluated the effectiveness of a social media-based intervention, designed around the core components of *The Guide* training package. The study involves all high schools in Ramhormoz city using a stratified random sampling method. A total of 204 students are expected to participate. Measures of mental health literacy and attitudes towards seeking professional psychological help are evaluated at three time points: before the intervention (baseline), 3 months, and 6 months after the intervention.

**Results:**

We anticipate a significant improvement in the mental health literacy score of the intervention group compared to the control group at post-intervention and both follow-ups. Additionally, we expect a substantial enhancement in the attitude towards seeking professional psychological help score for the intervention group compared to the control group at post-intervention and 6-month follow-up, though not at the 3-month follow-up.

**Conclusion:**

In conclusion, this study will contribute valuable insights into the effectiveness of social media-based interventions in enhancing mental health literacy and attitudes towards seeking professional help among high school students. The results will guide future initiatives in mental health education and promotion.

**Clinical trials:**

This study protocol is registered with the Iranian Registry of Clinical Trials (IRCT) under the registration number IRCT20230603058372N1, dated June 5, 2023. The study adheres to the Standard Protocol Items: Recommendations for Interventional Trials (SPIRIT) guidelines, as outlined in Supplementary File S1.

## Introduction

Adolescence, the transformative phase from childhood to adulthood, is marked by unique challenges, prominently among them the increasing prevalence of mental health issues both globally and within Iran. International studies underscore a significant proportion of adolescents worldwide grappling with mental health challenges such as anxiety and depression. In Iran, a recent meta-analysis indicates that the prevalence of depression among adolescents ranges from 10 to 18%, while anxiety disorders affect up to 30% of this population (World Health Organization, 2020; Kuek et al., 2023; Hoseini-Esfidarjani et al., 2022; Heizomi et al., 2020).

The transition from childhood to adolescence, characterized by heightened vulnerability, societal pressures, and evolving interpersonal dynamics, contributes to the complexity of mental health issues in this demographic. Recognizing the urgency of addressing these concerns, our study endeavors to contribute to the broader discourse on adolescent mental health literacy (MHL) through innovative and contextually relevant interventions (Heizomi et al., 2020; Jafari et al., 2021; Jorm, 2012; Patton et al., 2016).

Mental health literacy (MHL), defined as the knowledge and beliefs enabling the recognition, management, and prevention of mental disorders (Jorm, 2012), emerges as a critical determinant of mental health outcomes. It influences help-seeking behavior, aids in stigma reduction, and facilitates early intervention (Kitchener and Jorm, 2002). However, MHL is often inadequate among young people, particularly those at high risk of developing mental health problems (Bröder et al., 2017).

While school-based interventions have proven effective in improving MHL among adolescents (Anderson et al., 2022; Cairns and Rossetto, 2019), traditional approaches face challenges such as limited resources, time constraints, and low engagement. Consequently, there is a need to explore innovative and alternative methods to deliver MHL education in schools (Lehtimaki et al., 2021; Zsila and Reyes, 2023).

Social media, widely used and preferred by young people, presents a potential medium to enhance MHL education. Offering interactive and personalized features, it enables peer-to-peer communication and support (Zsila and Reyes, 2023; Arshad et al., 2019). However, it also poses risks and challenges, including privacy, ethical, and quality issues, as well as the potential negative impact on mental health (Raeside et al., 2022). This underscores the need to design and evaluate evidence-based, ethical, and engaging social media-based interventions for MHL education.

Building on the recommendations of global health organizations (World Health Organization, 2018; American Psychological Association Washington, 2023), our study leverages the pervasive influence of social media to enhance MHL among high school students in Ramhormoz city. The study protocol outlines a randomized controlled trial (RCT) designed to assess the effectiveness of an educational intervention delivered through social media in addressing specific mental health challenges faced by teenagers in this region.

The mental health care system for children and adolescents in Iran faces significant challenges, with a shortage of qualified professionals and unmet needs. Iran has less than 0.3 child psychiatrists per 100,000 children, reflecting a substantial gap in service provision, particularly in underserved areas (Zarafshan et al., 2021; Sharifi et al., 2016). Studies show that a high percentage of Iranian adolescents experience mental health issues, yet mental health care remains inadequate, particularly in lower-income regions (Sharifi et al., 2016). Furthermore, while there are efforts, such as UNICEF’s programs, to improve child mental health services, these interventions have limited reach and effectiveness in addressing the widespread need for mental health care (Zarafshan et al., 2021; Sharifi et al., 2016).

Ramhormoz, situated in the southwestern province of Khuzestan, Iran, serves as the focal point for our investigation. With a population of approximately 127,000 people primarily engaged in agriculture, the city retains a close-knit community feel, fostering interconnected relationships among its residents. While the penetration rate of social media is not known, it’s important to consider that owning a smartphone is a common criterion for participation in our study. Our deliberate choice of Ramhormoz as the study setting aims to unravel the nuanced interplay between traditional values, economic constraints, and the mental health landscape of its adolescents. By amalgamating insights from global prevalence trends, the unique socio-cultural context of Iran, and the evolving discourse on mental health literacy (MHL), our research aspires to contribute to the development of impactful strategies for promoting the mental well-being of adolescents in Ramhormoz city and beyond.

## Method/design

We used a CONSORT statement to describe the study – see Figure 1. The study design was a randomized controlled trial(RCT) with pre-test, post-test and control group without blinding. The participants will high school students from Ramhormoz city (Iran).

**Figure 1 fig1:**
[figure not shown]
CONSORT flow diagram illustrating participant allocation and progress through the trial.

### Sampling method

This study uses a stratified random sampling method that focuses exclusively on male participants aged 14–20 years. First, a school district is randomly selected from among the available districts. Within the selected district, schools are stratified and then randomly assigned to intervention and control groups. Three schools are assigned to the control group and three schools to the intervention group. A total of 102 male students will be randomly selected from all three schools in each group. The number of participants selected from each school will be proportional to the student population of that school, ensuring fair representation.

Male students were selected for this study due to specific cultural, religious, and logistical constraints. In the study setting, adolescent male students are the primary population with regular and independent access to mobile phones, a key requirement for participation in this digital communication-based intervention. Additionally, the male researcher’s access to female students’ mobile phone numbers is restricted by cultural norms and policies imposed by the Ministry of Education and Culture. These factors make the inclusion of female participants impractical within the framework of this study and necessitate a focus on male students to ensure the feasibility and integrity of the research design.

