#### Consent and assent collection process

##### To ensure ethical rigor and avoid potential coercion

*Parental Consent:* Consent was obtained electronically through an online form sent via parents’ mobile numbers provided by the school. Parents reviewed the study details and acknowledged their consent by clicking “agree.”*Adolescent Assent:* After parental consent was granted, adolescents were presented with a separate assent form within the online interface. They were individually informed about the study’s objectives, procedures, and voluntary nature in a private virtual setting. Adolescents had the opportunity to review and decide independently whether to participate by selecting “agree.”

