#### Inclusion/exclusion criteria

##### Inclusion criteria

To be eligible for this study, male students enrolled in public high schools in Ramhormoz city must meet the following criteria:

Have access to a smartphone with an internet connection.Demonstrate an understanding of both written and spoken Persian language.Express willingness to participate in the research and provide informed consent.Not having any known mental disorders or depressive symptoms.

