### Trial status

This trial is still in the planning stage and has not been implemented yet. The trial protocol has been approved by the Ethics Committee of Tehran University of Medical Sciences (IR.TUMS.SPH.REC.1402.075). The trial has been registered in the Iran Randomized Clinical Trial Center (IRCT20230603058372N1 on June 5, 2023). The recruitment of participants is expected to start in June 2023 and end in July 2023. The intervention phase is expected to start in August 2023 and end in September 2023. The follow-up phase is expected to start in November 2023 and end in January 2024. The data analysis and manuscript writing are expected to start in February 2024 and end in March 2024. The anticipated date of completion of the trial is April 2024.

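### Schools get their arm before students are selected in an unblinded trial, and nothing shown says the arm is withheld until consent, assent and baseline are complete

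*Protocol article*

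**What the plan says.** The Sampling method section sets out a sequence. A district is drawn. Then "Within the selected district, schools are stratified and then randomly assigned to intervention and control groups". The split is given next: "Three schools are assigned to the control group and three schools to the intervention group". Students come after that: "A total of 102 male students will be randomly selected from all three schools in each group", with each school's share proportional to its size.

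The Method/design section describes a randomised trial with "pre-test, post-test and control group without blinding".

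Entry depends on individual agreement. An inclusion criterion is "Express willingness to participate in the research and provide informed consent". On parents, the consent section says "Consent was obtained electronically through an online form"; the student's own assent follows. The information given to families covers, among other things, what taking part will involve.

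Baseline is an online questionnaire that students complete themselves before the intervention (Data collection). Its score is the covariate in the planned ANCOVA (Statistical analysis, under Potential confounds).

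On timing, the Trial status section says "The recruitment of participants is expected to start in June 2023 and end in July 2023". The intervention is to start in August, and the trial is described as still being planned.

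**The concern.** Randomising schools balances the schools in expectation. It does not balance which students within them agree to take part, if agreement is sought once the arm is set and can be known. The two arms also offer different things: fifteen online sessions over a month in one, and questionnaires with a printed guide at the end in the other. If families know which applies to them, the students who join may differ between arms in interest or motivation, and baseline answers may be coloured by what students expect to receive.

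The primary comparison is at stake. Intention-to-treat covers the students who entered; it cannot recover those who declined because of the arm. Baseline adjustment removes only the part of a difference that baseline MHLS captures, and a baseline answered with knowledge of the arm is itself an affected covariate. Recruiting more students would not remove the problem.

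**Working it through.** **1. The order of steps, side by side**

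| Step | Section | Position relative to school allocation |
|---|---|---|
| Schools assigned, three per arm | Sampling method | – |
| 102 students per arm drawn | Sampling method | After (stated) |
| Parental consent, then assent | Consent and assent collection process | Not stated; after, by inference |
| Baseline questionnaire | Data collection | Before the intervention (stated); after allocation, by inference |
| Disclosure of the arm to families | – | Not stated |

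The inference is short. Only a selected student can be consented and measured, and selection is stated to follow assignment. No text shown says that the allocation is concealed, that the arm is withheld until baseline closes, or that those who recruit are masked.

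**2. The yardstick: the plan's own figure**

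Inputs from Sample size calculation: SD 25.25, difference 12, two-sided 5%, power 80%, dropout 30%.

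n = 2 × [25.25 × (1.96 + 0.8416) / 12]² = 69.5, so 70 per arm. With dropout, 70 / 0.70 = 100, against the stated 102. The figure reproduces to within two students, so 25.25 and 12 are the right scale for the next steps.

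**3. An assumed shift on that scale**

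The article gives no consent rates, so the shift is an assumption, taken before any baseline adjustment.

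- 0.1 × 25.25 = 2.5 points; 2.525 / 12 = 21% of the target.
- 0.2 × 25.25 = 5.05 points; 5.05 / 12 = 42% of the target.

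**4. Could selective consent produce a shift of this order?**

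Suppose agreeing to take part follows a probit model whose latent variable has correlation ρ with baseline MHLS, and a proportion p agrees. The mean among those who agree then exceeds the mean of all those approached by SD × ρ × φ(z_p) / p. All values of p and ρ below are assumptions.

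- Consent selective in one arm only:
  - p = 0.90, ρ = 0.2: 25.25 × 0.2 × 0.1755 / 0.90 = 1.0 point.
  - p = 0.80, ρ = 0.5: 25.25 × 0.5 × 0.2800 / 0.80 = 4.4 points.
- Equally selective in both arms, at different consent rates:
  - 90% against 80%, ρ = 0.2: 0.98 − 1.77 = −0.8 points.
  - 90% against 70%, ρ = 0.5: 2.46 − 6.27 = −3.8 points.

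In the first case the selective arm has the higher mean. In the second, the arm with the higher consent rate has the lower mean. The direction therefore depends on facts that the article does not give.

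**5. What the planned analysis removes**

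The ANCOVA estimate is (follow-up difference) − b × (baseline difference), where b is the slope on baseline. It takes out the part of a selection effect that measured baseline MHLS carries, but not the part due to motivation that MHLS does not measure. If knowledge of the arm alone moves baseline answers by d points between arms, the estimate moves by −b × d.

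**The case against.** Several points on the other side are fair.

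- **Part of the order is inferred.** Only allocation followed by selection is written. The consent section orders parent before student and places neither relative to allocation; its past tense does not settle the matter. The flow diagram is not shown and could give another order. This stands, and the point is worded accordingly.
- **Allocated is not disclosed.** A reader might infer that families know their arm when they agree. The article does not say so. Being unblinded describes the design, not the moment of announcement, and the consent sections describe one information process with no arm-specific version. This makes the matter a risk and not a demonstrated bias.
- **Random selection protects in part.** Drawing students at random in proportion to school size limits whom the study approaches. It does not govern who agrees or how they answer.
- **Incentives and direction.** The data package is offered to participants without distinction by arm, which gives control families a reason to join. Fifteen sessions may deter as well as attract. Both points stand; neither rules out differential consent.
- **Who recruits.** A reader might infer that the person who recruits also runs the programme. The first author is named as facilitator, and the Sampling method section mentions a researcher's access to phone numbers, but no text says who recruits. The point does not rely on it.
- **Condensed article.** Details of concealment may sit in a fuller protocol. But the article does more than omit a detail: it states an order, and that order, followed as written, creates the exposure.

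**Conclusion.** The concern holds as a risk created by the stated sequence. Schools are assigned before students are selected, the trial is unblinded, entry depends on individual agreement, and no text shown keeps the arm back until consent, assent and baseline are complete. Intention-to-treat and baseline adjustment cannot fully repair differential recruitment.

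Size and direction cannot be determined from the article. Assuming a shift of 0.1 to 0.2 SD at the planned SD, it would be about 2.5 to 5.1 points, or 21% to 42% of the 12-point target. The consent model gives baseline differences of about 0.8 to 4.4 points in absolute value, also on assumed inputs. These figures show that the matter is not negligible on the trial's own scale; they do not estimate a bias.

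The conclusion rests on the inference that consent and baseline follow selection, and on the flow diagram not stating otherwise. The change should be made before recruitment.

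**What to change.** In the Sampling method section and the flow diagram, state this order:

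1. Select the six schools.
2. Draw the students in each, in proportion to school size.
3. Complete parental consent, student assent and the baseline questionnaire in all six schools during June-July, using the same arm-neutral information.
4. Draw or reveal the school allocation only once baseline has closed, and before the August start.

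If consent and baseline were always meant to come first, correcting the text to say so is enough. If the order cannot be changed, use identical arm-neutral invitations, mask those who recruit, and report the numbers selected, consenting and declining by school and arm. That would not remove the risk, but it would make it visible.

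The cost is small but not nil. No extra students are needed, and the planned recruitment window already precedes the intervention. Schools must commit before knowing their arm, in a trial that already expects some difficulty with school cooperation (Challenges and limitations), and someone must hold the allocation until baseline closes.

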### Sample size calculation

The main goal of this study is to determine the effect of education on the average score of mental health literacy in two intervention and control groups, which will be analyzed as the difference between the two averages. Since the minimum and maximum score of mental health literacy is between 29 and 130, therefore, the standard deviation of 25.25 points was considered and the number of samples in each group was determined in such a way that with 95% confidence and 80% test power, if the difference between the two averages A score greater than 12 is statistically significant. From the following formulas, the number of participants in each group was stated (Figure 2).

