**Figure 2 fig2:**
[figure not shown]
Sample size formula.

Therefore, for each of the intervention and control groups, 102 students will be randomly selected from among the second-high school students of Ramhormoz city (including 30% chance of dropping out). We try to select the number of people in each grade equally.

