
A high score for each attribute indicates a higher literacy rate for each attribute. Also, the total score of MHLS is obtained from the sum of the scores of all features. The lowest score is 29 and the highest is 130. Higher scores indicate more favorable MHL status. Based on the reliability results, MacDonald’s omega coefficient and Cronbach’s alpha coefficient for all MHLS features were 0.797 and 0.789, respectively.

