#### Potential confounds

Researchers anticipate several potential confounds that may influence the outcomes, such as:Pre-existing Mental Health Conditions: Variability in participants’ baseline mental health status may affect their response to the intervention.Socioeconomic Factors: Differences in socioeconomic status might influence participants’ access to mental health resources, potentially impacting outcomes.

The primary outcome of this study is the change in mental health literacy score (MHLS) from baseline to post-intervention and follow-up. The secondary outcome is the change in attitude towards seeking professional psychological help score from baseline to post-intervention and follow-up. Both outcomes will be measured using validated scales.

Demographic and baseline characteristics of the participants will be summarized using descriptive statistics, including mean, standard deviation, median, interquartile range, frequency, and percentage, as appropriate. The normality of the outcome variables will be assessed using graphical methods (histograms and Q-Q plots) and numerical tests (Shapiro–Wilk test). If the outcome variables are normally distributed, parametric tests will be employed; otherwise, non-parametric tests will be utilized.

Between-group differences in outcome variables at post-intervention and follow-up will be analyzed using analysis of covariance (ANCOVA), adjusting for baseline values and other potential confounders. Within-group changes in outcome variables from baseline to post-intervention and follow-up will be analyzed using paired t-tests or Wilcoxon signed-rank tests, depending on the normality assumption. Effect sizes and 95% confidence intervals will be reported for all comparisons.

We will employ techniques such as multilevel modeling (also known as hierarchical linear modeling) or generalized estimating equations (GEE) to model dependencies among observations within the same cluster. The level of significance for all statistical tests will be set at 0.05 (two-sided). All analyses will be conducted using SPSS software version 26.0.

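### The trial randomises three schools per arm, but its sample size is an individual-level calculation with no design effect, so the stated 80% power for 12 points does not hold at the stated SD without baseline adjustment

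*Protocol article*

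**What the plan says.** Under Sampling method, one district is chosen, and within it "schools are stratified and then randomly assigned to intervention and control groups". The split is explicit: "Three schools are assigned to the control group and three schools to the intervention group". Students are drawn only after that: "A total of 102 male students will be randomly selected from all three schools in each group", in proportion to school size. The school is therefore the unit of randomisation.

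Under Sample size calculation, the trial is sized on a difference between two means. The SD comes from the limits of the scale: "Since the minimum and maximum score of mental health literacy is between 29 and 130, therefore, the standard deviation of 25.25 points was considered". The target is "with 95% confidence and 80% test power, if the difference between the two averages A score greater than 12 is statistically significant". The result, given after Figure 2, is that "102 students will be randomly selected from among the second-high school students of Ramhormoz city (including 30% chance of dropping out"). The text mentions no intracluster correlation (ICC), design effect or number of schools.

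The analysis text (Statistical analysis, under Potential confounds) plans ANCOVA adjusted for baseline. It also plans multilevel modelling or GEE for dependence within clusters. The test level is fixed there: "The level of significance for all statistical tests will be set at 0.05 (two-sided"). The abstract and the Method/design section call the study a randomised controlled trial and do not say that it is cluster-randomised.

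**The concern.** Students in one school share teachers, peers and setting, so their scores are likely to be correlated. When schools are allocated, that correlation inflates the variance of the difference between arms. With only six schools, there is also little information from which to estimate the between-school variance. A calculation that treats the 204 students as independent overstates the information in the trial. Here the analysis section acknowledges clustering and the sample size does not.

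The power statement governs how a non-significant primary result will be read. If the real power for 12 points is well below 80%, a null result says much less about absence of effect than the protocol implies.

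The SD raises a second, separate question. It is a rule-of-thumb value from the theoretical range of the scale, so both the required number and any restated power rest on an input without data behind it.

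**Working it through.** **Inputs from the protocol article.** SD 25.25; difference 12; two-sided 5%; power 80%; dropout 30%; 3 schools per arm; 102 students per arm. **Assumed, because the document gives neither:** the ICC (0 to 0.10) and the correlation r between baseline and follow-up (0 or 0.5). Schools are treated as equal in size; unequal sizes would lower power a little further.

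**1. Reproducing the stated number.**
- Normal formula: n = 2 × (1.96 + 0.842)² × 25.25² / 12² = 69.5 per arm.
- The t-based version gives 70.5, so 71.
- Dropout: 71 / 0.7 = 101.4, rounded up to 102. (Using 70 gives 70 / 0.7 = 100.)

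The individual-level formula plus dropout uses up the whole of the stated 102. Figure 2 is not visible, but it cannot contain a design effect that changes this number.

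**2. Power with three schools per arm at the stated inputs.**
- Retained per arm: 102 × 0.7 = 71.4. Per school: m = 71.4 / 3 = 23.8.
- Design effect: DE = 1 + (m − 1) × ICC = 1 + 22.8 × ICC.
- Standard error: SE = 25.25 × √(2 × DE / 71.4).
- Noncentrality: 12 / SE. Degrees of freedom: 2 × (3 − 1) = 4.

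At ICC 0.05: DE = 2.14, SE = 6.18 and noncentrality = 1.94.

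| ICC (assumed) | DE | Power, t on 4 df | Power, normal approximation | Difference detectable with 80% power, t on 4 df |
|---|---|---|---|---|
| 0 | 1.00 | 57.5% | 81% | 15.9 |
| 0.01 | 1.23 | 50% | 73% | 17.6 |
| 0.02 | 1.46 | 44% | 65% | 19.2 |
| 0.05 | 2.14 | 32% | 49% | 23.3 |
| 0.10 | 3.28 | 23% | 35% | 28.8 |

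By the normal approximation, power drops below 80% once the ICC exceeds about 0.001. With no dropout at all (34 per school), that threshold is about 0.014, and the 4-df power is 60% at ICC 0.01 and 36% at 0.05.

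**3. Where the SD comes from.** (130 − 29) / 4 = 25.25 exactly. The Persian scale as described has 15 four-point items (8 + 2 + 3 + 2) and 14 five-point items (10 + 4). The article reports "alpha coefficient for all MHLS features were 0.797 and 0.789, respectively", the second figure being Cronbach's alpha. If 0.789 applies to the 29-item total:
- Sum of item variances / total variance = 1 − 0.789 × 28/29 = 0.238.
- Largest possible sum of item variances = 15 × 2.25 + 14 × 4 = 89.75, so SD ≤ √(89.75 / 0.238) = 19.4.
- Evenly spread item responses: 15 × 1.25 + 14 × 2 = 46.75, so SD ≈ √(46.75 / 0.238) = 14.0.

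**4. What a smaller SD and baseline adjustment would do.** Same design and dropout, difference 12, t on 4 df. Adjustment multiplies the SE by √(1 − r²), which is 0.866 at r = 0.5; this assumes that it reduces the within- and between-school parts alike.

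| SD | r | ICC 0.01 | ICC 0.02 | ICC 0.05 | ICC 0.10 |
|---|---|---|---|---|---|
| 25.25 | 0.5 | 61% | 54% | 40% | 29% |
| 19.4 | 0 | 71% | 64% | 49% | 35% |
| 19.4 | 0.5 | 82% | 75% | 60% | 44% |
| 14.0 | 0 | 92% | 88% | 75% | 57% |
| 14.0 | 0.5 | 97% | 95% | 85% | 69% |

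**The case against.** Four objections have weight.

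**The SD does not cause the shortfall.** A reader might infer that the rough SD is a second reason for low power. The article's own figures point the other way: 25.25 looks too large, and an overstated SD makes a sample size conservative. This stands, so the SD belongs in a separate remark about its source.

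**The figure of 19.4 is not a hard limit.** It needs alpha 0.789 to be that of the total score and to apply to these students. The wording refers to the features of the scale and is ambiguous, and alpha depends on the sample. It is a plausibility check only.

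**The low power is conditional.** A reader might conclude that the trial cannot reach 80%. The documents do not show that. Planned baseline ANCOVA and a smaller SD could together reach it: 82% at SD 19.4, ICC 0.01 and r = 0.5, or 88% at SD 14 and ICC 0.02 without adjustment. The ICC, true SD and r are all unknown here.

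**The document does not name a 4-df test.** It names multilevel modelling or GEE and fixes no small-sample method, which an analysis plan may supply. The 57.5% at zero ICC depends on that choice; the normal approximation gives 81%. At the stated SD without adjustment, however, both references fall below 80% at ICC 0.01 and above. With r = 0.5, the normal approximation at ICC 0.01 would be 84%, which is why the qualification about adjustment matters.

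The harm is also limited: the plan models clustering and reports 95% confidence intervals for all comparisons. The fault lies in the planning statement and not in the planned analysis.

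**Conclusion.** The concern holds in a bounded form. Schools are randomised, three per arm, and 102 per arm is an individual-level number with no design effect. At the protocol's own SD, difference and dropout, without baseline adjustment, the stated 80% is not delivered at any of the assumed ICCs from 0.01 to 0.10. Power there runs from about 50% down to 23% on 4 df, and from 73% down to 35% by the normal approximation. The difference detectable with 80% power on 4 df is about 18 to 29 points, not 12.

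Beyond those inputs, the power is unsupported; it is not proven to be inadequate. The arithmetic in the article is correct for an individually randomised trial; the fault is that it describes a different design from the one specified. The SD needs an empirical source, and a realistic value would probably improve the picture.

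**What to change.** Keep the 204 students and rewrite the Sample size calculation paragraph as a cluster-randomised calculation that states:
- 3 schools per arm and about 24 retained students per school;
- a small-sample reference distribution (4 df for a 3-versus-3 comparison);
- an assumed ICC range, such as 0.01 to 0.10, labelled as an assumption;
- an SD with an empirical basis, for example from the baseline data, in place of range/4;
- the baseline correlation on which the ANCOVA gain relies.

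Replace the claim of 80% power for 12 points with the resulting table of power or detectable differences, and describe the trial as cluster-randomised in the abstract and the Method/design section.

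The cost is wording and a less favourable stated power; no extra students are needed. Spreading the same students over more schools would raise power, but the documents do not show that enough eligible boys' schools exist in the selected district, so the fix does not depend on it.
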